## Abstract

**Background:**

Diabetes is one of the most common diseases worldwide and is associated with increased morbidity, mortality, and reduced quality of life. Many patients experience high diabetes-related distress as well as depression and anxiety symptoms, which are associated with poor diabetes self-management. As disease management is a central component in diabetes treatment, poor management enhances the occurrence of micro- and macrovascular complications. This emphasizes the relevance of reducing diabetes-related distress and providing adequate treatment options addressing the individual psychosocial burden of patients with diabetes. Since patients’ perspectives diverge significantly from those of practitioners in terms of relevant treatment aspects, the patient perspective on, for example, barriers to and facilitators of diabetes treatment is crucial for adequate and effective treatment as well as improvements to self-management and therefore, needs to be further explored.

**Objective:**

This study aims to examine diabetes-related distress, the course of distress throughout diabetes management, as well as barriers and facilitating factors in dealing with diabetes from the individual perspective of patients with type 1 and type 2 diabetes.

**Methods:**

The study employs a mixed methods design combining qualitative and quantitative data. Semistructured interviews (N=40) will be conducted with patients with type 1 diabetes (n=20) and patients with type 2 diabetes (n=20). The primary outcomes comprise (1) diabetes-related distress, (2) the severity of distress, (3) the course of distress throughout diabetes management, (4) barriers, and (5) facilitating factors. Questionnaires will provide data on the following secondary outcomes: diabetes-related emotional distress (the Problem Areas in Diabetes scale), symptoms of depression and anxiety (Patient Health Questionnaire, German version), personality functioning (Operationalized Psychodynamic Diagnosis-Structure Questionnaire), mentalizing capacities (Mentalization Questionnaire), epistemic trust (Epistemic Trust, Mistrust and Credulity Questionnaire) and experiences of child maltreatment (Childhood Trauma Questionnaire), and the overall health status of the patient (routine medical data).

**Results:**

As of April 2022, the conceptualization phase of the study was finalized. Ethics approval was received in January 2022 from the local ethics committee of the Justus Liebig University Giessen – Faculty of Medicine (AZ 161/21).

**Conclusions:**

This study will provide insights into the individual perspective of patients with type 1 and type 2 diabetes regarding their experiences with diabetes management and what they perceive to be relevant, obstructive, or beneficial. The insights gained could help further tailor diabetes treatment to the individual needs of patients with diabetes and therefore optimize diabetes self-management.

**Trial Registration:**

German Clinical Trial Register DRKS00024999; https://tinyurl.com/2wb4xdh8

**International Registered Report Identifier (IRRID):**

PRR1-10.2196/38477

## Introduction

With a global prevalence of 476 million, diabetes is one of the most common diseases worldwide [1]. About 10% of the German population has diabetes [2], with projections indicating a further increase [3]. Diabetes is associated with increased morbidity, mortality, and reduced quality of life [4] and poses growing socioeconomic challenges for the health care system (eg, medication and hospitalization) [5]. Regarding treatment, adequate glycemic control (glycated hemoglobin [HbA_1c_] <7.5%) and a high degree of self-management are crucial. However, studies have shown that approximately 58.4% of patients with type 1 diabetes and 40.4% of patients with type 2 diabetes do not achieve their target glycemic control [6]. Additionally, as many as 42% of patients with type 1 diabetes and 24% to 36% of patients with type 2 diabetes report pronounced diabetes-related distress [7] (defined as the emotional aspect of the burden of living with a mainly self-managed chronic disease) [8]. High diabetes-related distress is associated with inadequate glycemic control (HbA_1c_>7.5%) as well as poor diabetes management [9,10], highlighting the relevance of reducing this burden for patients with diabetes.

Further, patients with inadequate glycemic control present elevated depression or anxiety symptoms [11]. Diabetes has been shown to increase the risk of depressive symptomatology [7], while, conversely, depressive symptomatology increases the risk of developing type 2 diabetes by 34% [12]. Patients with diabetes have about twice the risk of developing an anxiety disorder compared to patients without diabetes, with fears of acute complications, such as hypoglycemia or subsequent diseases and complications (microvascular diseases like retinopathies as well as macrovascular diseases) [13]. The presence of psychiatric comorbidity is linked to both morbidity and mortality and decreased quality of life [7], while health care costs and the risk of subsequent diseases are augmented [14]. Since psychological distress and psychiatric comorbidities not only require adequate treatment by themselves but also accelerate the development of diabetes-associated secondary diseases and worsen their course [15], they pose a significant treatment focus in patients with diabetes.

As strict monitoring and regulation of glycemic control are central in diabetes management, factors associated with poor glycemic control are important to consider. Evidence on the association between poor glycemic control and, for example, depression or anxiety symptoms is inconsistent. Some studies showed an association between depression and anxiety symptoms and poor glycemic control in adults with type 1 diabetes [16], while others found no association between depression and poor glycemic control [17,18]. This might be a conceptual issue, as the notion of diabetes-related distress better describes the psychosocial adjustment to diabetes than depression, comprising anger, guilt, frustration, denial, and loneliness [19]. Both constructs seem to overlap and correlate, yet are distinct [20,21], potentially explaining why pharmacological and psychological treatments for patients with depression and type 1 and type 2 diabetes yield inconsistent achievements regarding glycemic control [22,23]. Recently, a multidisciplinary, psychosomatic, psychodynamically oriented, short-term intervention improved glycemic control by focusing on individuals’ specific diabetes-related distress [24]. This emphasizes the need to align treatment with individual needs. Studies have shown that the focus of patients and practitioners diverges; patients mainly focus on the importance of diabetes in their daily life whereas practitioners almost exclusively orient toward measurable parameters [25]. This might hinder adequate diabetes management and affect the success of treatment options. Hence, to individualize interventions, further research on patients’ perspectives and their diabetes-related distress is needed.

The first aim of this study is to explore individual and specific issues in diabetes management in patients with poor glycemic control in order to better understand barriers and facilitators in their treatment. Based on qualitative data, we will derive patients’ perspectives on individual diabetes-related burdens, critical times in the course of their treatment, as well as barriers and support factors. The secondary outcomes will be measured with questionnaires addressing diabetes-related distress in the context of diabetes and treatment requirements, psychological aspects (depression and anxiety symptoms, personality functioning, mentalization capacities, epistemic trust, and experiences of child maltreatment), as well as physical health assessed through routine medical data (diabetes type; HbA_1c_; medication; weight and height; total cholesterol, low-density lipoprotein (LDL) and high-density lipoprotein (HDL) cholesterol, triglycerides; and previous illnesses).

## Methods

### Study Design

The study will be conducted using an explorative mixed methods design and will integrate qualitative as well as quantitative data. Patients between 18 and 69 years with diagnosed type 1 or type 2 diabetes, with an HbA_1c_ value >7.5%, a diabetes duration of minimum 2 years, a completed diabetes self-management program, sufficient German language skills, and cognitive abilities will be included in the study. Patients with type 3 diabetes or gestational diabetes, severe comorbid diseases (eg, dementia, major depressive disorder, psychosis, or addiction), a diabetic foot, and those who are bedridden or are care-dependent patients will be excluded from the investigation.

Figure 1 illustrates the procedure of the study. Recruitment will take place in a clinic that specializes in diabetes. In step 1, the clinic will be equipped with all relevant documents (eg, information on the course of the study, data protection, form for assessing routine medical data, flyer and information for patients, and questionnaires). In step 2, patients will be asked by clinic personnel to participate in the study or made aware of the study by a flyer. In step 3, patients willing to participate in the study will be given comprehensive information, be informed verbally on the study purpose and procedure, and be assigned an interview appointment by the clinic personnel. In addition, self-report questionnaires will be handed out. In step 4, the researchers conducting the interviews will thoroughly discuss the patient information and the declaration of consent with the patient. After providing written informed consent, the interview will be conducted in the clinic. Due to the ongoing COVID-19 pandemic, the patient interviews will be conducted under strict compliance with the clinics’ hygiene regulations by researchers who are familiar with proper patient contact and the special regulations in effect under the pandemic.

**Figure 1 figure1:**
[figure not shown]
Schematic illustration of the study procedure.

### Sample Size

A total of 40 patient interviews (20 each for type 1 and type 2 diabetes) will be conducted. Among those, 4 interviews (2 each for type 1 and type 2 diabetes) are planned as a pretest to gain a deeper understanding of whether the developed guideline will work or if questions need to be reevaluated and modified.

### Assessment

#### Interview Guideline

Semistructured interviews will be conducted based on an interview guideline, with each section containing open questions, giving the participant the opportunity to speak openly and introduce new content.

##### Phase 1: Welcome

The participant will be greeted and—corresponding to the patient information—the interviewer will explain the interview as well as the protection of privacy, including pseudonymization of the data and how the transcript will be handled. After obtaining written informed consent and providing time for questions, the interviewer will start the audio recording and begin to collect sociodemographic information.

##### Phase 2 – Category I: Diagnosis and Course of Diabetes

This category aims to collect information on the patients’ experience with the initial diagnosis, difficult phases including symptoms of depression and anxiety, or diabetes-associated complications, as well as less difficult or good phases regarding diabetes. Sample questions include: “In your opinion, what went badly [when receiving the diagnosis]?” and “What memorable events were there in connection with diabetes and the treatment of diabetes (eg, complications and medication changes)?”

##### Phase 3 – Category II: Diabetes-Related Distress and Burden

In this category, individual diabetes-related distress and burden, including concerns and behavior changes, will be explored. Sample questions include: “What is it that worries you most about your diabetes?” and “What new experiences—positive and negative—have you had that you might not have had without diabetes?”

##### Phase 4 – Category III: Barriers and Facilitators

Questions of this category investigate barriers, for example, through doctors, the use of external support offers, as well as difficulties at work and in the social environment. Sample questions include: “What difficulties have arisen in the workplace?” and “Are there any tools (blood sugar diaries, food diaries, or apps) that make it easier for you to deal with diabetes?”

##### Phase 5: Final Phase

The participant will have the opportunity to tell the interviewer a specific recommendation that they believe to be useful for every patient with diabetes. After time for additional questions, the participant will be thanked for their time and participation.

#### Problem Areas in Diabetes Scale

The Problem Areas in Diabetes scale [26] includes 20 items to assess different areas of diabetes-related emotional distress. The response options range from 0 (“no problem”) to 4 (“major problem”). A sum score is computed and multiplied by 1.25, resulting in a total score between 0 and 100. Higher values represent more severe distress. A value >39 indicates severe emotional distress [19], pointing to significant depressive symptoms [26,27].

#### Patient Health Questionnaire

The Patient Health Questionnaire (German version; PHQ-D) measures depressive and anxiety syndromes, somatoform syndromes, eating disorders, alcohol abuse, psychosocial functioning, stressors, critical life events, menstruation, pregnancy, and childbirth, and shows good validity [28,29]. The depression module of the PHQ-D corresponds to the PHQ-9 [30]. By providing response options between 0 (“not at all”) and 3 (“almost every day”), it allows the calculation of a total score between 0 and 27, with severity classified as no depressive disorder, <5 points; mild depression, 5-9 points; moderate depression, 10-14 points; and severe depression, 15-27 points [30,31]. Anxiety syndromes are assessed with a panic module and a scale for other anxiety syndromes. The panic module consists of a general part on anxiety attacks (questions 3a-d) and a part with questions that refer specifically to the last severe anxiety attack (questions 4a-k). The possible answers are “yes” and “no.” A panic syndrome is expected when questions 3a to 3d are answered with “yes” and at least 4 of the questions 4a to 4k are answered with “yes.” Other anxiety syndromes (questions 5a-g) have the response options “not at all,” “some days,” and “more than half the days.” Another anxiety syndrome is assumed if question 5a is answered with “more than half of the days” and at least 3 of the questions 5b to 5g are answered with “more than half of the days” [32].

#### Childhood Trauma Questionnaire

Different forms of child maltreatment will be assessed with the Childhood Trauma Questionnaire (CTQ). Participants answer questions regarding sexual, emotional, and physical abuse as well as emotional and physical neglect on a scale with response options ranging from 1 (“not at all”) to 5 (“very often”). Each subscale consists of 5 items, resulting in sum scores from 5 to 25. Severity is classified as none to minimal, low to moderate, moderate to severe, and severe to extreme [33]. The German version of the CTQ [34] shows good internal consistency, except for physical neglect (sexual abuse: α=.89; physical abuse: α=.80; emotional abuse: α=.87; physical neglect: α=.55; and emotional neglect: α=.83).

#### Operationalized Psychodynamic Diagnosis-Structure Questionnaire

The Operationalized Psychodynamic Diagnosis-Structure Questionnaire (OPD-SQS) is a self-report questionnaire to screen for participants with deficits in personality functioning. It comprises 3 subscales (ie, self-perception, interpersonal contact, and relationship model) with 4 items in each scale. Response options range from 0 (“does not apply at all”) to 4 (“fully applies”), resulting in a sum score from 0 to 48, with higher scores indicating impairments in personality functioning. The OPD-SQS showed good internal consistency (α=.88) [35].

#### Mentalization Questionnaire

The Mentalization Questionnaire [36] is a self-report instrument to assess mentalization capacities from the patient’s perspective. It consists of 15 items with response options ranging from 1 (“no agreement at all”) to 5 (“total agreement”). Analyses yielded 4 subscales with acceptable reliability and sufficient validity: (1) refusing self-reflection, (2) emotional awareness, (3) psychic equivalence mode, and (4) regulation of affect. The sum score ranges from 15 to 75, with higher scores indicating lower mentalization capacities.

#### Epistemic Trust

The Epistemic Trust, Mistrust and Credulity Questionnaire by Campbell and colleagues [37] was developed as a self-report questionnaire to assess epistemic trust, distrust, and gullibility. It comprises 15 items with response options ranging from 1 (“strongly disagree”) to 7 (“strongly agree”) [38], resulting in a score from 15 to 105. High epistemic trust, mistrust, and credulity are indicated by either strong agreement or strong disagreement with the statement.

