### Outcome Parameters

Primary outcomes: qualitative data from semistructured interviews will comprise (1) diabetes-related distress; (2) severity of diabetes-related distress; (3) general distress at the time of diagnosis notification, medication change, if applicable, and special events regarding the patients’ social environment; (4) barriers; and (5) facilitating factors. Secondary outcomes include quantitative data that will comprise self-report questionnaire data to assess (1) diabetes-related emotional distress and (2) psychological aspects (depression and anxiety symptoms, personality functioning, mentalization capacities, epistemic trust, and child maltreatment), as well as (3) routine medical data (diabetes type, HbA_1c_, medication, weight, height, total cholesterol, LDL and HDL cholesterol, triglycerides, and preexisting conditions).

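### The epistemic trust questionnaire is given one 15 to 105 total over three named constructs, with no stated direction, so that total does not measure the listed outcome

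*Protocol article*

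**What the plan says.** The Epistemic Trust section of the protocol article says that the instrument "was developed as a self-report questionnaire to assess epistemic trust, distrust, and gullibility", which makes three constructs. On format it says "It comprises 15 items with response options ranging from 1", with 7 as the top code, "resulting in a score from 15 to 105". On direction it offers one sentence: "High epistemic trust, mistrust, and credulity are indicated by either strong agreement or strong disagreement with the statement". It mentions no subscale score, reverse-keyed item or cut-off, and does not say what a higher total means.

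Outcome Parameters places the result among the secondary outcomes as one of the "psychological aspects (depression and anxiety symptoms, personality functioning, mentalization capacities, epistemic trust, and child maltreatment". Mistrust and credulity are not named there.

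The neighbouring scales are handled differently. For the OPD-SQS the article gives a total "resulting in a sum score from 0 to 48, with higher scores indicating impairments in personality functioning". For the Mentalization Questionnaire it says: "The sum score ranges from 15 to 75, with higher scores indicating lower mentalization capacities". The Problem Areas in Diabetes scale also has a stated direction, and the Childhood Trauma Questionnaire is scored by subscale, 5 to 25 each.

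**The concern.** A sum over items that measure different things is useful only if the items share a direction and the sum has a stated meaning. Here trust and mistrust are opposed by name, credulity is listed as a third quantity, and neither the sign of each item nor the meaning of the total is given. An analyst who follows the text gets a number labelled epistemic trust that need not rise with trust.

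At stake is the description of this one secondary outcome in 40 patients, 20 per diabetes type. If a mean total were reported for each type, a reader could not tell whether the higher one meant more trust, more mistrust or more credulity. If the scoring is settled only after the data are seen, the choice among versions is also open to influence from the results.

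**Working it through.** **Inputs from the document.** 15 items, codes 1 to 7, three constructs, one stated range of 15 to 105 (Epistemic Trust section).

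**Assumed, because the document does not give them.** The number of items per construct and the keying of items. Both are varied below.

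**Step 1: reproduce the stated range.** 15 × 1 = 15 and 15 × 7 = 105. The range is arithmetically right, and it fits only a single sum over all items.

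**Step 2: extreme profiles, 5 items per construct.** Let a profile be full agreement (7) with every item of one construct and full disagreement (1) with the rest. A reversed item scores 8 minus the response. Terms are in the order trust + mistrust + credulity.

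| Keying (assumed) | Trust only | Mistrust only | Credulity only |
|---|---|---|---|
| No item reversed | 35 + 5 + 5 = 45 | 5 + 35 + 5 = 45 | 5 + 5 + 35 = 45 |
| Mistrust items reversed | 35 + 35 + 5 = 75 | 5 + 5 + 5 = 15 | 5 + 35 + 35 = 75 |
| Mistrust and credulity items reversed | 35 + 35 + 35 = 105 | 5 + 5 + 35 = 45 | 5 + 35 + 5 = 45 |

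Answering 4 throughout gives 15 × 4 = 60 under every keying. With no reversal, all three profiles fall below that neutral value. Reversing the mistrust items separates trust from mistrust, but the wholly trusting and the wholly credulous profile then tie at 75. Only the third keying ties trust to neither, and the document does not state it.

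**Step 3: unequal splits, no reversal.** A profile that is maximal on a construct with k items scores 7k + (15 − k) = 15 + 6k. This depends on the number of items and not on which construct it is: k = 3 gives 33, k = 4 gives 39, k = 7 gives 57, k = 9 gives 69. Trust and mistrust tie whenever they have equally many items. If they do not, the gap reflects item counts only.

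**Step 4: what a given total says about trust.** With 5 items per construct, the trust items contribute 5 to 35 and the other ten contribute 10 to 70, whatever their keying. A total of 60 requires the other ten to contribute 60 − 35 = 25 up to 60 − 5 = 55, all possible. A total of 60 therefore fits any trust score from 5 to 35, its full range. Over the splits tried (7/4/4, 4/7/4, 4/4/7, 9/3/3, 3/9/3, 3/3/9) only 9/3/3 narrows this, to 18 to 54 out of 9 to 63.

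These are logical limits, not expected distributions. Any sum of subscales has some of this looseness. What sets this scale apart is that the OPD-SQS and Mentalization Questionnaire totals each refer to one named construct and have a declared direction, and this total has neither.

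**The case against.** The strongest reply is that the direction sentence concerns responses to an individual statement, so it may only be a clumsy way of saying that keying differs by item. That stands. A reader might infer that totals of 15 and 105 would both count as high, but the sentence does not speak of the total, so the document does not support this. Item-specific keying would also remove the tie between trust and mistrust, so the 45 = 45 result needs no reversed items as well as an equal split. It does not rescue the total: the text does not say which items are reversed, and credulity stays in the sum with no sign.

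A reader might also call all three constructs mutually opposed. Only trust and mistrust are opposed by name; nothing in the document makes credulity the opposite of either.

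It can further be said that a condensed article leaves subscale scoring to a fuller document, that nothing rules subscales out, and that the short outcome label is shorthand for the whole instrument, since the Abstract pairs the label with the questionnaire's full name. This has some force, and the label alone would not be worth raising. But the article does state a score and a direction rule for this instrument, and neither can be used as written. That is a defective statement, not an omitted detail.

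**Conclusion.** The point holds in a limited form. The 15 to 105 total, as described, does not identify the level of epistemic trust, and no direction for it is given. The example of 45 for both maximal trust and maximal mistrust rests on 5 items per construct and no reversed items. The wider conclusion does not depend on those assumptions, because no keying or sign is stated under which the sum would mean trust.

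A reader might conclude that the secondary outcome itself cannot be interpreted. The document does not support that: the item responses are collected, so construct scores can be derived at any time before analysis. No test, threshold, eligibility rule or specific comparison uses this score; Quantitative Data Analysis plans only descriptive and exploratory work, and the primary outcomes come from the interviews. Severity is therefore minor to moderate.

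**What to change.** In the Epistemic Trust section, replace the 15 to 105 total with three separate scores for trust, mistrust and credulity, computed with the instrument's published item key. State the range of each score and what a higher value means. Replace the sentence on agreement or disagreement with that statement of direction, and identify any reverse-keyed items. In Outcome Parameters, name the three scores in place of the single label. Settle this before the questionnaire data are analysed.

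The cost is a few sentences and a changed scoring line in SPSS. The questionnaire, its items and the burden on patients stay the same.
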